# Reliability, validity and objectivity of the data collection instruments

All instruments to be used in this project are standard instruments, with proven content validity and reliability, with Cronback alpha greater than .80 for each set.

# Interventions

#### Experimental arm:

###### Brief intervention

Participants who are randomized in the intervention arm receive personalized feedback on their AUDIT results, a health education leaflet (Annex 6), plus brief counselling about reducing excessive drinking, during a one session 20 minute intervention.

The steps of brief counselling are: 1) Identify any alcohol related problems mentioned in the interview, 2) Introduce the sensible drinking leaflet, and emphasise the idea of sensible limits, and make sure that patients realize that they are in the medium-risk drinking category, 3) Work through the first 3 sections of the problem solving manual while mentioning the value of reviewing the other sections, 4) Describe drinking diary cards 5) Identify a helper, and 6) mention the 3, 6 and 12 months follow-up. The brief intervention will be based on the WHO brief intervention package for hazardous and harmful drinking^36^. The Information-Motivation-Behavioural Skills (IMB) Model

will be used to guide the alcohol reduction intervention in South Africa.

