###### Control arm:

Participants randomized to this group will not receive feedback on the initial alcohol screening. They will be provided with a health education leaflet on responsible drinking (Annex 6), and they will only receive the brief intervention after the 12 month follow-up if the intervention has proved to be efficacious.

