| 3. How often do you have (for men) five or more and (for women) four or more drinks on one occasion?  Never  Less than Monthly  Monthly  Weekly  Daily or almost daily  ***Skip to question 9 and 10 if Total Score for Qs 2 and 3 is =0*** | | (0)  (1)  (2)  (3)  (4)  [___] | 8. How often during the last 3 months have you been unable to remember what happened the night before because you had been drunk?  Never  Less than monthly  Monthly  Weekly  Daily or almost daily | | | (0)  (1)  (2)  (3)  (4)  [___] |
| 4. How often during the last 3 months have you found that you were not able to stop drinking once you had started?  Never……………………………………………………  Less than monthly……………………………………..  Monthly………………………………………………….  Weekly…………………………………………………..  Daily or almost daily…………………………………... | | (0)  (1)  (2)  (3)  (4)  [___] | 9. Have you or someone else been injured as a result of your drinking?  No……………………………………………….  Yes, but not in the last 3 months…………….  Yes, during the last 3 months……………….. | | | (0)  (2)  (4)  [___] |
| 5. How often during the last year have you failed to do what was normally expected from you because of drinking?  Never……………………………………………………  Less than monthly……………………………………..  Monthly………………………………………………….  Weekly…………………………………………………..  Daily or almost daily………………………………… | | (0)  (1)  (2)  (3)  (4)  [___] | 10. Has a relative or friend or a doctor or another health worker been concerned about your drinking or suggested you to cut down?  No……………………………………………….  Yes, but not in the last 6 months…………….  Yes, during the last 6 months……………….. | | | (0)  (2)  (4)  [___] |
| Record total of specific items here [____] | | | | | | |

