#### Alcohol consumption-SeTswana

| **The Alcohol Use Disorders Identification Test (AUDIT):**  **Interview Version- Tswana** | | | | | | |
| --- | --- | --- | --- | --- | --- | --- |
| Molwetsi yo o rategang,  Jaana ka e nngwe ya ditsela tseo ke di dirisang go tlhatlhoba maemo a mathata a tsamaisanang le tsa pholo mo botshelong jwa gago. Kitso eo ke tla e fitlhelang e botlhokwa ka gore e tla nthusa go neelana ka thuso kana go oka le tlhokomelo e e kwa godimo. Gore ke kgone go dira seno, ke tla kopa gore o orabe dipotso tse di latelang ka tiriso ya nnotagi mo dikgweding tse thataro tse di fetileng. Dikarabo tsa dipotso tseo di tla beng di boditswe di tla nna mo sephiring. Mo pampiring ya dipotso ga go kitla go ntshiwa sepe se se amanang le leina la gago.  **Age:** ____ Dingwaga **Gender:** [1] Monna [2] Mosadi **Letlha*:*** ____/ ____/ _______  Nnotagi e e lekaneng e: | | | | | | |
| *[figure not shown]* | *Thoto e le nngwe ya sepiriti (whisky, gin & vodka) (e.g., 25ml at 43%)* | *[figure not shown]* | *Galase e le nngwe ya lekaraese*  *(e.g., 25ml at 30%)* | | | |
| *[figure not shown]* | *Khene e le nngwe ya bojalwa*  *(e.g., 340ml at 5%)* | *[figure not shown]* | *Galase e le nngwe ya beine*  *(e.g., 120ml at 12%)* | *[figure not shown]* | *Katone e le nngwe ya bojalwa ba setho*  *(e.g., 500ml at 3%)* | |
| 1. Ke ka makgetlho a le makae o ne o nwa seno se se nang le bojalwa mo dikgweding tse thataro tse di fetileng?  Le goka [*tlolela go Qs 9-10*]……………………….  Kgwedi kana kwa tlase……………………………....  Gabedi go ya go gane mo kgweding……………….  Gabedi go ya go gararo mo bekeng……................  Gane kgotsa go feta mo bekeng…………………. | | (0)  (1)  (2)  (3)  (4)  [__] | 6. Ke ga kae mo dikgweding tse thataro tse di fetileng mo o neng o tlhoka nnotagi fela mosong go tlosa letsapa la nno e ntsi e o nnileng le yone mo bosigong jo bo fetileng?  Le goka...........................................................  Mo tlase ga kgwedi.........................................  Kgwedi nngwe le nngwe.................................  Beke nngwe le nngwe....................................  Tsatsi lengwe le lengwe................................. | | | (0)  (1)  (2)  (3)  (4)  [__] |

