**Gopola seno:**

Nnotagi e lekaneng ke e latelang:

[figure not shown]

Thoto e le nngwe fela ya sepiriti (e.g., 25ml at 43%)

Khene e le nngwe fela ya bojalwa (e.g., 340ml at 5%)

[figure not shown]

[figure not shown]

Galase e le nngwe ya beine.(e .g., 120ml at 12%)

[figure not shown]

Galase e le nngwe ya lekaraese. (e.g., 25ml at 30%)

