**Alcohol Standard Units**

| *[figure not shown]* | *A single tot of spirits (whisky, gin & vodka) (e.g., 25ml at 43%)* |
| --- | --- |
| *[figure not shown]* | *1 can of ordinary beer*  *(e.g., 340ml at 5%)* |
| *[figure not shown]* | A small glass of liqueur or aperitif *(e.g., 25ml at 30%)* |
| *[figure not shown]* | *1 glass of wine*  *(e.g., 120ml at 12%)* |
| *[figure not shown]* | *Cartoon of ordinary commercial sorghum beer*  *(e.g., 500ml at 3%)* |

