**Appendix 1: Health Education Leaflet English**

HEALTH EDUCATION LEAFLET: What constitutes risky drinking?

Excessive drinking can result in:

Difficulty coping with stress

Relationship problems

Stomach problems

Diarrhoea

Sleeplessness

Falls or other accidents

Arrest for drinking under the influence of alcohol

Financial problems

Feeling confused after drinking

Depression

Memory loss

Problems with medications

Automobile accidents

Feeling alone or left out because of drinking

High blood pressure

Trembling hands

Malnutrition

Seizures

Cancer

Stroke

Drinking too much alcohol can hurt your health, your behaviours, and your relationships. You may have experienced some of the problems shown at the left, which may be related to your use of alcohol.

Remember:

Sensible drinking are:

Women:

- No more than 2 drinks per day
- Do not drink at least 2 days a week

Men:

- No more than 3 drinks per day
- Do not drink at least 2 days a week

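### The English health education leaflet gives a standard tot of spirits as 52 ml, while both AUDIT forms, the unit table and the Setswana leaflets give 25 ml, so its spirits limit is about twice the intended volume

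*Protocol*

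**What the plan says.** The leaflet belongs to both arms. In the protocol's Interventions section, the experimental arm receives feedback on the AUDIT result, the Annex 6 leaflet and one counselling session, whose second step is to "Introduce the sensible drinking leaflet, and emphasise the idea of sensible limits". Of the control arm the protocol says: "They will be provided with a health education leaflet on responsible drinking (Annex 6").

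The leaflet headed "Appendix 1: Health Education Leaflet English" states its limits as counts of drinks. For women, and again for everyone over 65, it reads "No more than 2 drinks per day"; for men the figure is three. It then lists what one standard drink is, and there a single tot of spirits is 52 ml at 43%.

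Everywhere else the same drink is 25 ml at 43%. The Alcohol Standard Units table in Annex 6 has "A single tot of spirits (whisky, gin & vodka) (e.g., 25ml at 43"%). The Setswana AUDIT has "Thoto e le nngwe ya sepiriti (whisky, gin & vodka) (e.g., 25ml at 43"%). The Setswana leaflet has "Thoto e le nngwe fela ya sepiriti (e.g., 25ml at 43"%), and its two further copies at the end of Annex 6 repeat the figure. The English AUDIT in Annex 3 also gives 25 ml at 43%.

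**The concern.** A limit expressed in drinks has no meaning in volume or alcohol until the drink is defined. With two definitions of the same beverage in the trial's own materials, the spirits limit given to a participant depends on the leaflet language. In the English version it errs in the unsafe direction. The participants are HIV-positive medium-risk drinkers, and the leaflet is meant to tell them what is sensible.

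There is also a consistency problem with the outcome measure. AUDIT items 2 and 3 count drinks, and the English AUDIT form defines the spirits drink as 25 ml. The leaflet taught to the same participants gives a different size. The AUDIT is repeated at 3 and 12 months, and the alcohol use score is the variable analysed for the treatment-by-time interaction.

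**Working it through.** **Inputs, all from the protocol**

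| Place | One tot of spirits |
|---|---|
| Annex 6, English leaflet | 52 ml at 43% |
| Annex 3, English AUDIT | 25 ml at 43% |
| Setswana AUDIT | 25 ml at 43% |
| Annex 6, Alcohol Standard Units | 25 ml at 43% |
| Annex 6, Setswana leaflet (three copies) | 25 ml at 43% |

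That is one place against six. Beer (340 ml at 5%), wine (120 ml at 12%) and liqueur (25 ml at 30%) agree throughout, and so does sorghum beer (500 ml at 3%) wherever it is listed. Spirits is the only drink whose size differs.

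**Step 1. Ratio of the two sizes.** 52 / 25 = 2.08.

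**Step 2. Pure alcohol per tot (volume × strength).**
- 52 × 0.43 = 22.36 ml
- 25 × 0.43 = 10.75 ml

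**Step 3. Which figure fits the rest of the list.** Pure alcohol in the other listed drinks:
- beer: 340 × 0.05 = 17.0 ml
- sorghum beer: 500 × 0.03 = 15.0 ml
- wine: 120 × 0.12 = 14.4 ml
- liqueur: 25 × 0.30 = 7.5 ml

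A 25 ml tot (10.75 ml) lies inside the range 7.5 to 17.0 ml. A 52 ml tot (22.36 ml) lies above it and would be the strongest standard drink on the leaflet. This supports 25 ml as the intended figure, and 52 is 25 with the digits swapped.

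**Step 4. Daily spirits limit (drinks per day × volume per drink).**

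| Group | Drinks per day | As printed (52 ml) | At 25 ml | Pure alcohol, printed against intended |
|---|---|---|---|---|
| Men | 3 | 156 ml | 75 ml | 67.1 against 32.3 ml |
| Women, and all over 65 | 2 | 104 ml | 50 ml | 44.7 against 21.5 ml |

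**After the correction.** With 25 ml in the English leaflet, the daily spirits limits become 75 ml and 50 ml. These match the Setswana leaflets and use the AUDIT drink size.

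**The case against.** The case for treating this as minor is a good one, and much of it stands.

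- It is almost certainly a typing error in one cell of an annex. That explains the figure, but the cell is in a participant handout that forms part of the intervention, so the printed content is still wrong.
- The volume is given as an example beside a tot. A reader who counts tots and ignores millilitres gets the same limit from either version. This stands, so the doubling applies only to readers who go by the printed volume.
- The Alcohol Standard Units table in Annex 6 is also in English and gives 25 ml, so some English readers may see both figures. This softens the error but leaves the handout contradicting its companion table.
- Counsellors are trained, supervised and work from a manual that is not shown. It cannot be said that they would teach 52 ml.

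A stronger reading is tempting. Someone who counts by the leaflet at follow-up would report about half as many drinks with no change in drinking. Take a man who drinks 150 ml of spirits on one occasion a week: 150 / 25 = 6.0 drinks becomes 150 / 52 = 2.88. AUDIT item 2 then falls from 2 to 1 and item 3 from 3 to 0, which is 4 points. For a woman at 100 ml, 100 / 25 = 4.0 drinks becomes 100 / 52 = 1.92. Items 2 and 3 together fall from 4 to 0, which triggers the instruction "Skip to question 9 and 10 if Total Score for Qs 2 and 3 is =0". Because only the intervention arm is walked through the leaflet, a reader might infer a difference between arms that looks like efficacy.

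The documents do not support that inference. The AUDIT is an interview that opens with its own 25 ml definition and is repeated at each visit, and the follow-up assessor is blinded to allocation. The participant would have to recall a millilitre figure from a leaflet given 3 or 12 months earlier and apply it over the definition on the form. Both arms receive the same leaflet. The two examples are spirits-only drinkers placed where the change of size matters most. A doubled limit would also weaken the intervention, so even the net direction is not established.

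**Conclusion.** The English leaflet is wrong as written. It contradicts six other statements of the same drink size in the protocol and overstates the spirits volume within sensible limits by a factor of 2.08: 156 ml instead of 75 ml for men, and 104 ml instead of 50 ml for women and those over 65. It also disagrees with the drink size used to score the AUDIT.

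This rests on three assumptions: that 25 ml is the intended figure, that the leaflet named in counselling step 2 is the Annex 6 leaflet, and that the reader goes by the printed volume. It concerns only spirits drinkers who are given the English leaflet. The protocol does not give their share, so no trial-level effect can be stated.

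An effect on follow-up AUDIT scores is possible but not shown, and bias between the arms should not be claimed. The fault is small and local, but it lies in the content of the intervention and is worth correcting.

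**What to change.** In the English leaflet in Annex 6, change the tot of spirits from 52 ml to 25 ml at 43% before printing. The leaflet then agrees with the Setswana leaflets, the Alcohol Standard Units table and both AUDIT forms. The description of the counselling steps needs no change. The cost is one corrected figure, with no effect on participants' visits, the sample size, the analysis or the budget, provided it is done before the leaflets are printed.

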###### Control arm:

Participants randomized to this group will not receive feedback on the initial alcohol screening. They will be provided with a health education leaflet on responsible drinking (Annex 6), and they will only receive the brief intervention after the 12 month follow-up if the intervention has proved to be efficacious.

###### Counselor Training and Intervention Quality Assurance

The intervention research assistant will deliver the interventions to patients as per usual clinic services. There is a comprehensive manual for the brief intervention which will be used to guide the research assistant counselor throughout the session. The research assistant counselors had been trained to administer the intervention protocol through role playing and general skills training techniques in a 5 day workshop for the earlier trial, and will receive two additional days training for HIV and sexual related questions. Site visits will be done bi-weekly by one of the investigators and project members to offer support and supervision to the trained research assistant counselors.

# Data Analysis

*Definition of virological failure:*

We follow the definition used in the national guidelines in which virological failure is defined as a repeat VL ≥ 1000 copies/ml after intense adherence assessment^38^.

*Definition of immunological failure:*

Immunological failure is defined according to the WHO definition. Failure is defined as a fall of CD4 count to pretherapy baseline (or below), *or* a 50% fall from the on-treatment peak value (if known) *or* a persistent CD4 levels below 100 cells/mm^3^.^39^

Means, standard deviations, and percentages will be used for descriptive statistics. T-test for continuous data and chi-square for categorical data will be used to examine differences between groups. Generalized Linear Model Repeated Measures 2 x 3 Analysis of Variance (ANOVA) will be used for comparing observations (alcohol use score) across the three contact periods to demonstrate a treatment intervention x time interaction.Observations with a single follow-up point missing (at either 3 and 12 months) will be imputed with the available follow-up. Data for participants who are lost to follow-up at 3 and 12 months will be imputed using baseline values. SPSS for Windows version 18.0 (SPSS, Inc., Chicago, IL) will be used for calculations.

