#### Hypotheses:

- HIV positive patients who are medium risk drinkers in the intervention group decrease drinking more than those in the control group;
- The levels of alcohol consumption of patients in the intervention group will continuously reduce over a 12 month assessment period;
- In the intervention group, adherence levels to ART during follow up will be higher, alcohol consumption lower, quality of life and health status better and number of therapies failing virologically or immunologically will be lower compared to the control group at post intervention;

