#### Inclusion criteria

-HIV 1 positive male and female patients

-Outpatients

-18 years and above

-No mental impairment

-Medium risk drinkers (i.e. 8-19 for men and 7-19 for women on the AUDIT questionnaire)

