#### Sample size calculation

The sample size was calculated using Open Epi (available on www.openepi.com), for a two arm randomized controlled trial. With 80% power, a significance level of 5%, two sided-tests, assuming that adherence levels to ART overall are 90% in Africa. The adherence level of moderate alcohol users compared to abstainers and minimal alcoholusers shows an odds ratio of 0.480^27^. The minimum sample size for each group is 251 patients. To accommodate a drop-out rate of 10% overall, the sample size for each group will be 276, making a total of 552 patients.

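### Copying baseline or the other visit into missing AUDIT scores distorts the arm comparison and the 3-to-12-month course, by an amount that depends on drop-out and on how far scores fall

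*Protocol*

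**What the plan says.** The Data Analysis section of the protocol sets two rules. For one missing visit: "Observations with a single follow-up point missing (at either 3 and 12 months) will be imputed with the available follow-up". This works in both directions, so a 12-month score can stand in for the 3-month score and the reverse. For both visits missing: "Data for participants who are lost to follow-up at 3 and 12 months will be imputed using baseline values". The completed alcohol use scores go into a 2 x 3 ANOVA "across the three contact periods to demonstrate a treatment intervention x time interaction". The section names no missing-data assumption and no sensitivity analysis for these rules.

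Three other places bear on the point:

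- Entry is restricted by the baseline score itself: "Medium risk drinkers (i.e. 8-19 for men and 7-19 for women on the AUDIT questionnaire" (Inclusion criteria).
- Objectives 4 and 5 ask for arm comparisons at 3 and at 12 months, and a hypothesis concerns the time course: "The levels of alcohol consumption of patients in the intervention group will continuously reduce over a 12 month assessment period".
- The only drop-out figure is in the Sample size calculation: "To accommodate a drop-out rate of 10% overall, the sample size for each group will be 276". It is not split by arm or by visit.

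**The concern.** Copying baseline declares that a lost patient did not change. In this trial that is an unlikely average. Patients enter because their baseline AUDIT is raised, so some fall is expected in both arms through regression to the mean, and the control arm also receives the leaflet. The copied baseline is then too high on average. If one arm loses more patients than the other, that arm looks worse for a reason unrelated to the intervention. If both lose the same share, a true effect is diluted.

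Copying between visits is a separate problem and needs no imbalance between arms. It sets the 3-to-12-month change to exactly zero for each patient with one missing visit, while the protocol wants the two visits compared separately and hypothesises a continuing reduction. Most items of the English AUDIT in Annex 3 ask about the last 3 months. A 12-month score therefore mainly describes roughly months 9 to 12, and the rule may enter it as the 3-month result.

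**Working it through.** **Inputs from the protocol.** Both copy rules and the arm x time test (Data Analysis); 10% overall drop-out and 276 per arm (Sample size calculation); two-sided 5% level (same section). The protocol gives no expected AUDIT change, no SD and no drop-out by arm. These are assumed below and varied.

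**The plan's own figure.** 90% adherence is odds of 9; 9 x 0.480 = 4.32; 4.32/5.32 = 81.2%. Comparing 90% with 81.2% at 80% power gives 250.02 by the Kelsey formula, rounded up to the stated 251; 251 x 1.1 = 276.1, the stated 276. The figure reproduces, but it is built on adherence. It says nothing for or against the AUDIT imputation.

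**Baseline rule, closed form.** Let m be an arm's mean change and d its drop-out, and suppose drop-outs would have changed like completers in their arm. Filled patients contribute zero change, so

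- estimated difference = (1 - dT) x mT - (1 - dC) x mC
- bias = dC x mC - dT x mT

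Equal drop-out: the estimate is (1 - d) x (mT - mC). At d = 10%, a true effect of 1.5 becomes 0.90 x 1.5 = 1.35.

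No true effect, both arms change by -4: with drop-out of 5% (intervention) and 15% (control), 0.95 x (-4) - 0.85 x (-4) = -0.40, in favour of the intervention. With the split reversed it is +0.40, against it.

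True difference of -1 (changes of -5 and -4):

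| Drop-out intervention / control | Estimated difference |
|---|---|
| 10% / 10% | -0.90 |
| 5% / 15% | -1.35 |
| 15% / 5% | -0.45 |

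**Type I error, closed form, one visit.** Assume an SD of change of 5. The variance of the filled change in an arm is (1 - d) x 25 + d x (1 - d) x m². For m = -4 and drop-out 5% / 15%, the variances are 23.75 + 0.76 = 24.51 and 21.25 + 2.04 = 23.29. The standard error is the square root of 47.80/276, or 0.416. The bias of 0.40 is 0.96 standard errors, which gives 16.1% rejections. For m = -2 the result is 7.8%, and for m = -6 it is 28.5%. Equal drop-out gives 5.0% throughout.

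**Type I error, simulated with the planned ANOVA interaction.** Assumptions: population AUDIT mean 8, SD 6, reliability 0.6, selection to 8-19, 276 per arm, no true effect, drop-out unrelated to outcome, baseline copied to both visits. Under these inputs regression to the mean produces a fall of 1.7 points. The larger falls add a common drop of 2 or 4 points in both arms.

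| Common fall | 10% / 10% | 12% / 8% | 15% / 5% |
|---|---|---|---|
| 1.7 (regression to the mean only) | about 5% | 5.0% | 6.7% |
| 3.7 (further 2 points) | about 5% | 5.9% | 14.0% |
| 5.7 (further 4 points) | about 5% | not run | 27.1% |

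The first row at 15% / 5%, taken with the closed-form 7.8% for a 2-point fall, is what is meant by about 7-8%. The bias at a fall of 3.7 is about 0.10 x 3.7 = 0.37 points. An analysis of observed scores stays at about 5% under the same drop-out mechanism.

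**Copying between visits.** Let D3 and D12 be the true effects, with a share k of each arm missing month 12 only and a share k missing month 3 only. Then

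- 12-month estimate = (1 - k) x D12 + k x D3
- 3-month estimate = (1 - k) x D3 + k x D12
- 3-to-12-month contrast = (1 - 2k) x (D12 - D3)

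With k = 10%, D3 = -2 and D12 = 0, the estimates are -0.2 at 12 months and -1.8 at 3 months. The contrast falls from 2.0 to 1.6, a loss of 20%. The 10% per single visit is an assumption.

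**The case against.** The strongest reply is that material inflation needs two things together: a large imbalance in drop-out and a large common fall. The protocol supports neither as a figure. It plans for 10% loss overall, at least six contact attempts, renewed attempts at the next follow-up, and visits at the usual HIV-care intervals (Procedure). With 12% versus 8%, type I error barely moves. Under equal drop-out the rule only dilutes a true effect, which is conservative for a superiority claim. If patients who resume drinking are the ones who leave, returning them to baseline is arguable, and a mixed model is biased too.

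All of this stands, and it limits the size of the problem. It does not rescue the rules. A difference in drop-out is plausible, since only the intervention arm has a counselling session in which the follow-up visits are mentioned and a helper is named, and the analysis offers no protection if one occurs. The rule is also not reliably conservative: with falling scores, extra loss in the control arm favours the intervention.

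A reader might further infer that treating copied values as real data inflates the false-positive rate by itself. The calculations do not bear this out for the arm comparison. With equal drop-out, and a further 10% of patients copied across visits, the interaction test still rejects 5.0% of the time under no effect. The inflation comes from bias.

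**Conclusion.** The point holds in a conditional form, as something that should be fixed. The protocol itself prescribes the copy rules, so this is a stated method and not a detail left for a later analysis plan. The baseline rule dilutes a true effect by the drop-out share and, with unequal drop-out and falling scores, shifts the arm difference by about the drop-out difference times the mean fall. The cross-visit rule conflicts directly with the separate 3- and 12-month comparisons and with the hypothesis of continuing reduction, though only for patients missing exactly one visit.

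Two stronger readings are not supported. One is that the arm difference is biased whenever drop-out differs: if the missing patients' scores would not have changed on average, copying baseline adds no bias. The other is that the trial faces a 14% or 27% false-positive rate: those figures require an assumed threefold drop-out imbalance and a common fall well beyond regression to the mean. With regression to the mean alone the figure at that imbalance is about 7-8%, and at milder imbalances it stays near the nominal 5%. Every AUDIT change, SD and drop-out split used here is an assumption.

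**What to change.** Replace the two imputation sentences in Data Analysis. State that the AUDIT analysis is a likelihood-based mixed model on the observed 3- and 12-month scores, with arm, visit and their interaction, baseline AUDIT as a covariate, and no copied values. Keep the present copy rules as a sensitivity analysis, labelled as such, and report drop-out by arm and visit beside it.

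The cost is a few sentences of wording. Data collection and sample size do not change, and SPSS, the package already named, offers such models (MIXED). The downside is that the model relies on data being missing at random. If patients who relapse are the ones who leave, it is biased as well; the retained sensitivity analysis helps to show how far the conclusion depends on that.
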